**Figure 1 F1:**
[figure not shown]
**Participant flow chart.** Notes: 1. ABMUHB – Abertawe Bro Morgannwg University Health Board; CDDFT – County Durham and Darlington NHS Foundation Trust. 2. The patient or next of kin is approached for consent in the afternoon if verbal and written information about the trial is provided in the morning, or the following day if provided in the afternoon. 3. Investigational medicinal product; either 21 capsules of probiotic or placebo.

Demographic and clinical data will be recorded at recruitment and include the type and dose of antibiotics and other potential risk factors for AAD or CDAD (Table 2).

**Table 2 T2:** Baseline demographic and clinic data and risk factors for AAD

**Variable**	**Units or Categories where appropriate**
· Age	years
· Sex	male; female
· Race	white; black; Asian; Chinese; other
· Period of recruitment	summer (May – Sept); winter (Oct-March)
· Smoking	usual number of cigarettes/day
· Alcohol	usual number of units/week
· Where admitted from	home; residential care; other hospital; other
· Admission type	emergency/unplanned; elective/ planned for procedure or investigation
· Admission diagnosis or main cause of admission	
· Co-morbidity	hypertension; asthma; diabetes; chronic obstructive airways disease; renal disease; irritable bowel syndrome; dementia; Alzheimer’s disease; other
· Previous GI surgery	
· Number of hospital admissions in last eight weeks	
· Antacid treatment	antacid; H_2_-receptor antagonist; proton pump inhibitor
· Naso-gastric tube *in-situ*	
· Duration of hospital stay prior to recruitment	days
· Indication for antibiotic treatment	
· Antibiotic treatment: antibiotic used^1^	single class; 2 classes; 3 or more classes
· Antibiotic treatment: total duration	single dose; 1–6 days; 7–13 days; ≥14 days

^1^Antibiotics will be classified according to British National Formulary categories (http://www.bnf.org): Penicillins (sub-classified as benzylpenicillin, penicillinase resistant penicillin, broad-spectrum penicillins, anti-pseudomonas penicillins); Cephalosporins (sub-classified as 1^st^, 2^nd^ and 3^rd^ generation); Carbapenems and other beta-lactams; Tetracyclines; Aminoglycosides; Macrolides; Clindamycin; Sulphonamides and trimethoprim; Metronidazole; Quinolones; Glycopeptides; TB drugs; other.

### Generation and concealment of a random allocation sequence

A random allocation sequence using blocks of variable sizes will be produced using SAS PROC PLAN Version 9.1 (SAS Institute Inc., Cary, NC, USA). The sequence will allocate participants to either placebo or probiotic on a 1:1 basis and be stratified by centre to ensure that similar numbers of patients will be allocated to each arm of the study in each centre. The allocation sequence will not be available to members of the research team during participant recruitment and follow-up.

The process for acquiring a license for provision of the IMPs was begun in March 2008 and a Medicines and Healthcare products Regulatory Agency (MHRA) inspector notified in April 2008. The MHRA inspected the facility responsible for the packaging and quality control of the IMPs and the license was granted in November 2008. We had underestimated the time required for MHRA approval and this resulted in a delay in starting participant recruitment.

To ensure the quality of the probiotic, organism identity will be checked by established molecular techniques and viability by quantitative bacterial culture in study preparations retrieved from wards during the study. This will be done by an independent laboratory to maintain masking of the allocation sequence. *In vitro* antibiotic testing demonstrated that the probiotic bacteria were generally sensitive to broad spectrum antibiotics and all four strains were sensitive to ceftriaxone, chloramphenicol, erythromycin, linezolid and tetracycline.

### Follow-up

Research nurses will review participants daily during admission to determine the onset, frequency and duration of any diarrhoea and ask about gastrointestinal symptoms (abdominal pain, bloating, flatus, nausea), acceptability and adverse effects of the interventions. After discharge, follow-up will be weekly by telephone call, postal questionnaire or home visit as appropriate. Participants will be provided with contact details for ready telephone access to research staff to notify the onset of diarrhoea or adverse events. All participants will be followed-up for 8 weeks after completing antibiotic treatment to a maximum of 12 weeks from recruitment for those on longer antibiotic courses.

### Outcome measures

The two outcomes used to generate the sample size, AAD and CDAD, have been identified as co-primary outcomes (Table 3). Diarrhoea is defined as 3 or more loose stools in a 24 h period. We will use the Bristol Stool Form Scale [29] to assist participants in describing stool consistency; types 5-7 will be consistent with diarrhoea.

**Table 3 T3:** Outcome measures

**Primary outcomes**	1. the occurrence of AAD
	2. the occurrence of CDAD
	1. severity^1^ and duration of AAD
	2. severity^1,2^ and duration of CDAD and incidence of recurrence within the 8-12 weeks follow-up period
	3. abdominal symptoms (abdominal pain, bloating, flatus, nausea)
**Secondary outcomes**	4. well-being and quality of life assessed using the generic measures EQ-5D and the York SF12 (Iglesias 2001) at recruitment and 4 and 8 weeks
	5. duration of hospital stay
	6. serious adverse effects
	7. acceptability of the probiotic preparation
	8. viability of the probiotic at point of administration
	9. cost-effectiveness

^1^Frequency and consistency of stools. ^2^Additional information extracted from the clinical records (*e.g.* laboratory parameters, findings at sigmoidoscopy, pseudomembraneous colitis, colectomy, death).

All participants who develop diarrhoea during the study period will be asked to provide a stool sample and this will be collected during a home visit if required. The cause of diarrhoea will be determined by NHS laboratories according to their usual practice. Stools will be analysed for diarrhoeal pathogens (bacterial culture for *Salmonella* sp, *Shigella* sp, Campylobacter, *E. Coli* 0157; wet film for ova, cysts and parasites) and for *C. difficile* toxins. In ABMUHB, *C. difficile* will be identified by an in-house culture assay with further analysis by Meridian Premier Toxin A + B Enzyme Immunoassay (Meridian Bioscience Europe Inc., Cincinnati, USA) if required. In CDDFT, toxins are identified using the mini VIDAS system (C. diff Quik Check, Techlab, Blacksburg, U.S.A.). If a cause of the diarrhoea is not identified, a further stool sample will be collected and tested 2 days later.

For the primary outcome measures, AAD is defined as diarrhoea without pathogens detected on routine laboratory analysis, negative for *C. difficile* toxin and without alternative cause (e.g. laxative treatment). CDAD is defined as diarrhoea with stools positive for *C. difficile* A or B toxin. For quality control purposes, *C. difficile* culture and confirmation by immunoassay will be undertaken in 1 in 5 *C. difficile* toxin positive stool samples collected in Swansea. In view of the known inadequacies of current methods for the laboratory diagnosis of *C. difficile *[30], we will also save stool samples at −20°C from participants with diarrhoea for further testing for the glutamate dehydrogenase antigen and also lactoferrin (IBD scan and C. diff Quik Chek Complete; Alere Limited, Stockport, UK). This may result in the diagnosis of CDAD that was not detected by routine methods.

Participants who develop severe diarrhoea will be investigated and managed according to the current practice of their clinicians. We will extract information from the clinical records (*e.g.* laboratory parameters, findings at sigmoidoscopy, colectomy) to classify the severity of CDAD. At the end of follow-up, participants will be classified as either developing AAD, CDAD, another cause of diarrhoea (*e.g.* norovirus) or no diarrhoea. Other endpoints have been listed as secondary outcomes (Table 3).

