## Background

Antibiotic-associated diarrhoea (AAD) is diarrhoea that occurs in association with antibiotic treatment and without an alternative cause [1]. It is estimated to occur in 5 – 39% of people taking antibiotics during or up to 12 weeks after treatment [2]. AAD varies markedly in severity from mild diarrhoea to severe diarrhoea as part of a life-threatening illness caused by the anaerobic bacterium *Clostridium difficile* (*Clostridium difficile* associated diarrhoea*;* CDAD) which accounts for 15–39% of cases of AAD [3]. A particular concern is the emergence of the hypervirulent ribotype 027 strain of *C. difficile* documented in Canada, USA and Europe [4]. Even mild diarrhoea may cause significant morbidity and prolong hospital stay. The annual healthcare cost of CDAD in the USA was estimated to be more than $3 billion [5,6].

Host risk factors for AAD include advanced age, immune suppression, gastrointestinal disease or previous gastrointestinal surgery and severe co-morbidity [2,3,7]. AAD can complicate treatment with any antibiotic but broad spectrum antibiotics (clindamycin, cephalosporins, β-lactamase resistant penicillins, quinolones), antibiotic combinations and repeated or long treatment courses are associated with the greatest risk of AAD [2,7]. Other environmental factors include admission to hospital, longer duration of stay and use of naso-gastric tubes [8]. Suppression of gastric acid may also be an additional risk factor for CDAD in both hospital inpatients [9] and people in the community [10].

Antibiotics may result in diarrhoea through several mechanisms. Antibiotic disruption of the commensal gut microorganisms results in osmotic or secretory diarrhoea from changes in carbohydrate, short chain fatty acid and bile acid metabolism and impaired colonization resistance allowing a competitive growth advantage to diarrhoeagenic organisms [11-13].

Given the frequency and potential severity of CDAD, extensive and costly strategies for the prevention of AAD have become an established part of hospital in-patient management. These include strict limitations on the use of antibiotics, hand washing, isolation of diarrhoea patients and decontamination of the environment [14]. However, despite these efforts, the heat- and drying-resistant spores of *C. difficile* persist in the modern hospital environment [15,16].

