In view of the mechanisms underlying AAD, probiotics offer a potential means of prevention. Probiotics are defined as live microbial organisms which, when administered in adequate numbers, are beneficial to health [17]. In a recent meta-analysis, McFarland [18] pooled data from 25 RCTs (total of 2,810 adults and children) and reported a reduced relative risk of AAD in participants receiving a probiotic (0.43; 95% CI 0.31 – 0.58). Trials of many different single strains of probiotic bacteria, the yeast *Saccharomyces boulardii (S. boulardii*)*,* probiotic mixtures and probiotic and prebiotic mixtures were included in this analysis. Dosage (number of organisms) also varied markedly between studies. In sub-group analyses, factors associated with greater efficacy in preventing AAD were use of *S. boulardii* or *Lactobacillus rhamnosus (L. rhamnosus) GG*, mixtures of probiotics and preparations with high numbers of organisms.

Members of our research group [19] assessed the effect of a combination of *L. acidophilus* and *B. bifidum* on CDAD in a pilot study in elderly patients receiving antibiotics. Overall, 30/138 (22%) patients developed diarrhoea with 5/69 in the placebo group and 2/69 in the probiotic group testing positive for *C. difficile* toxin. In this small study, the main effect of the intervention appeared to be neutralisation of the toxin rather than prevention of colonization with *C. difficile*. The meta-analysis by McFarland [18] included 5 studies, in addition to our study, but all of these were treatment trials of patients with established or recurrent CDAD. When designing our study, apart from a small trial with few CDAD cases [20], we were not aware of other studies that had assessed probiotics in the primary prevention of CDAD in hospitalized adults. Since then, reports of trials have been consistent with the prevention of CDAD by lactobacilli and bifidobacteria although relatively small numbers of participants were recruited [21,22].

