### Sample size and recruitment

Conservatively, we expected ADD to occur in 20% and CDAD in 4% of participants allocated to the placebo group [2]. To detect a 50% reduction in the frequency CDAD in the probiotic group (i.e. 2% frequency) with 80% power at the 5% significance level, would require 2,478 subjects (1,239 in each group; 1:1 allocation). At the 5% significance level, this number of participants would provide a power of ≫99% to detect a 50% reduction in ADD (i.e. 10% frequency) and a power of 90% to detect a 25% reduction in ADD (i.e. 15% frequency) in the probiotic group. To allow for 10% drop-outs and 10% loss to follow-up due to deaths unrelated to diarrhoea, we plan to recruit 2,974 participants.

Based on data from 2005/6, about 14,000 patients per year aged ≥65 years and exposed to antibiotics were admitted to the study hospitals and there was a total of 963 cases of CDAD. Conservatively, we expect to be able to recruit between 1:9 and 1:10 of eligible patients (approximately 124 patients/month) and undertake recruitment for a total of 24 months. This estimate was supported by a 2-week pilot study of the recruitment process in 23 medical and surgical wards in Morriston Hospital when research nurses visited the wards daily. Out of a total of 253 admissions aged ≥65 years, 166 patients were excluded (152 patients had no current or planned exposure to antibiotics; 12 already had diarrhoea [including 1 CDAD]; 1 active inflammatory bowel disease; 1 reported a previous adverse reaction to a probiotic). Eighty-seven (34.4%) patients were eligible to participate in the pilot study but 8 of these were either confused or not available (in theatre or undergoing investigations). Therefore, the study design was explained to 79 patients (31.2% of total admissions) and 58 (73.4%) stated that they would have agreed to participate in this study.

We will monitor the number of participants reaching study endpoints in each hospital every 3 months. The ethical permission secured for the study included all hospitals within each health authority providing an ability to extend recruitment if needed.

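### AAD includes C. difficile diarrhoea in the Background but excludes it in the co-primary definition; the 90% AAD power may belong to the wider outcome, and the two co-primaries can trade cases

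*Protocol article*

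**What the plan says.** The article uses AAD in two senses.

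- **Inclusive.** The Background describes AAD as running from mild diarrhoea to life-threatening *C. difficile* illness, and says of CDAD "which accounts for 15–39% of cases of AAD". It takes the overall AAD frequency of 5–39% from reference 2.
- **Exclusive.** For the primary outcomes, Outcome measures states: "AAD is defined as diarrhoea without pathogens detected on routine laboratory analysis, negative for" *C. difficile* toxin and without another cause. At the end of follow-up each participant is assigned to AAD, CDAD, another cause or no diarrhoea.

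Sample size and recruitment, again citing reference 2, says: "Conservatively, we expected ADD to occur in 20% and CDAD in 4% of participants allocated to the placebo group". (ADD is evidently a misprint for AAD.) The trial is sized on CDAD falling from 4% to 2% and "would require 2,478 subjects (1,239 in each group; 1:1 allocation". For AAD it then claims power well above "99% to detect a 50% reduction in ADD (i.e. 10% frequency") and "a power of 90% to detect a 25% reduction in ADD".

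On mechanism, the Background reports of the group's pilot that "the main effect of the intervention appeared to be neutralisation of the toxin rather than prevention of colonization with" *C. difficile*. The section on the investigational products lists in vitro toxin neutralisation among the reasons for choosing the preparation.

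**The concern.** There are two consequences.

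First, if the 20% counts all antibiotic-associated diarrhoea, the stated AAD power describes an outcome wider, and so more frequent, than the one the trial will analyse.

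Second, the exclusive definition makes the co-primaries compete. If the probiotic neutralises toxin in a participant who nevertheless has three or more loose stools in a day, with no other pathogen or cause found, that participant no longer meets the CDAD definition and does meet the AAD definition. A gain on one co-primary could then appear as a loss on the other. This does not depend on how the 20% is read. The Abstract's hypothesis is that the probiotic prevents antibiotic-associated diarrhoea, so what a result on the AAD co-primary means is at stake.

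**Working it through.** **Inputs** (Sample size and recruitment): placebo rates AAD 20% and CDAD 4%; 1,239 per arm; 5% significance, taken as two-sided because the article does not say.

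**Formula.** With p̄ = (p1 + p2)/2 and n per arm,

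power = Φ{ [ |p1 − p2| − 1.96·√(2p̄(1 − p̄)/n) ] / √[ (p1(1 − p1) + p2(1 − p2))/n ] }.

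The continuity-corrected form subtracts 1/n from |p1 − p2|.

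**Step 1: reproduce the article's figures.**
- Sample size, 4% v 2%, 80% power: [1.96·√(2·0.03·0.97) + 0.8416·√(0.04·0.96 + 0.02·0.98)]² / 0.02² = 1,141 per arm. With continuity correction, (1,141/4)·[1 + √(1 + 4/(1,141·0.02))]² = 1,239, exactly as stated.
- AAD 20% v 15%: (0.05 − 0.02992)/0.01523 = 1.318, power 90.6% (89.7% corrected). Stated: 90%.
- AAD 20% v 10%: above 99.99%. Stated: well above 99%.

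The arithmetic is right for its inputs.

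**Step 2: which AAD is the 20%?**
- The shared citation is the main evidence for the inclusive reading.
- The ratio does not discriminate. Inclusive gives 4/20 = 20% and exclusive gives 4/24 = 16.7%; both lie within 15–39%.
- The pilot is compatible with the inclusive reading. It had 30/138 = 21.7% with any diarrhoea. If the 5 + 2 = 7 toxin-positive patients are among the 30, toxin-negative diarrhoea is 23/138 = 16.7%. These figures pool both arms and are not the source cited for the 20%.

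**Step 3: AAD power if the 20% includes the 4%.** Toxin-negative AAD is 20 − 4 = 16%.
- 25% reduction, 16% v 12%: (0.04 − 0.02732)/0.01392 = 0.911, power 81.9% (80.3% corrected).
- 50% reduction, 16% v 8%: above 99.9%.

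**Step 4: cases moving from CDAD to AAD.** The article gives no rate. The extreme case assumes that the whole 2-point CDAD reduction (4% to 2%) reappears as toxin-negative diarrhoea, on top of a true 25% reduction in the other cases.

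| Reading of the 20% | No move | Full move | AAD power, full move |
|---|---|---|---|
| Includes CDAD | 16% v 12% | 16% v 14% | (0.02 − 0.02812)/0.01434 = −0.566, 28.6% |
| Excludes CDAD | 20% v 15% | 20% v 17% | (0.03 − 0.03058)/0.01559 = −0.037, 48.5% |

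**Step 5: the inclusive outcome.**
- First row with full move: total AAD is 16 + 4 = 20% v 14 + 2 = 16%. (0.04 − 0.03025)/0.01541 = 0.633, power 73.6%.
- Effect on CDAD only, toxin-negative AAD unchanged at 16%: total is 20% v 18%. (0.02 − 0.03089)/0.01576 = −0.691, power 24.5%.

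**The case against.** The other side has good points.

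- **The 20% may already be toxin-negative.** Sample size and recruitment lists AAD and CDAD as separate rates, and Outcome measures calls these the outcomes behind the sample size. No sentence says that one contains the other, and the cited source is not at hand. This stands: the inclusive reading is an inference.
- **The stated power is not an arithmetic error.** A reader might infer that the calculation is wrong or the trial undersized. Neither follows. The figures reproduce, CDAD sets the sample size, and 80–82% still matches the power the trial was sized for. Lower values can be produced by making CDAD 39% of a 20% total, but that implies 39% × 20% = 7.8% CDAD, against the stated 4%.
- **Movement of cases is possible, not shown.** A reader might infer that the AAD outcome is biased against the probiotic and would show false harm. With neutralisation alone and no diarrhoea prevented (16% v 18%), AAD would be significant against the probiotic in about 26% of trials. That requires every averted CDAD case to go on having toxin-negative diarrhoea. If neutralising the toxin prevents the diarrhoea, nothing moves. The pilot evidence is 5/69 v 2/69, and the article itself hedges it.
- **There are partial safeguards.** Stored stools will be retested and may reveal further CDAD, and the total can be recovered by adding the exclusive classes. But a total computed only after results are known lacks the standing of a prespecified analysis.
- **Separate classes have a purpose.** They stop a CDAD effect from driving the AAD result. This is a fair reason to keep toxin-negative AAD as a reported component.

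**Conclusion.** The point holds in a limited form. The two meanings of AAD are on the page and need reconciling, because a co-primary outcome and its power depend on which applies.

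If the 20% includes the 4% CDAD, which is probable but unstated, the 90% power for a 25% reduction should read about 80–82%. The power for a 50% reduction and the sample size are unaffected.

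The possible trade between co-primaries exists on either reading, since the article itself relies on toxin neutralisation. Its size is unknown. AAD power of 29% (or 49% if the 20% excludes CDAD) is the limit under complete movement of the averted CDAD cases, not an expected value.

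**What to change.** Before unblinding:

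1. State whether the 20% planning rate includes CDAD.
2. Prespecify total AAD including CDAD. Preferably make it the AAD co-primary, since it is the outcome the Background describes. Otherwise make it a named supporting analysis to be read alongside both co-primaries. Report toxin-negative AAD as a component.
3. If the toxin-negative definition stays as co-primary, restate its power from the matching placebo rate (about 16% if the 20% is inclusive).

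**Cost.** No new data, participants or procedures are needed. The inclusive outcome overlaps with CDAD, so the two co-primaries would be correlated. It also has low power (about 24%) if the probiotic affects CDAD only. The article reports that recruitment began in June 2009, so a change of co-primary would have to be documented as made blind to allocation. The supporting-analysis option leaves the co-primaries as they are.

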### Sample size and recruitment

Conservatively, we expected ADD to occur in 20% and CDAD in 4% of participants allocated to the placebo group [2]. To detect a 50% reduction in the frequency CDAD in the probiotic group (i.e. 2% frequency) with 80% power at the 5% significance level, would require 2,478 subjects (1,239 in each group; 1:1 allocation). At the 5% significance level, this number of participants would provide a power of ≫99% to detect a 50% reduction in ADD (i.e. 10% frequency) and a power of 90% to detect a 25% reduction in ADD (i.e. 15% frequency) in the probiotic group. To allow for 10% drop-outs and 10% loss to follow-up due to deaths unrelated to diarrhoea, we plan to recruit 2,974 participants.

Based on data from 2005/6, about 14,000 patients per year aged ≥65 years and exposed to antibiotics were admitted to the study hospitals and there was a total of 963 cases of CDAD. Conservatively, we expect to be able to recruit between 1:9 and 1:10 of eligible patients (approximately 124 patients/month) and undertake recruitment for a total of 24 months. This estimate was supported by a 2-week pilot study of the recruitment process in 23 medical and surgical wards in Morriston Hospital when research nurses visited the wards daily. Out of a total of 253 admissions aged ≥65 years, 166 patients were excluded (152 patients had no current or planned exposure to antibiotics; 12 already had diarrhoea [including 1 CDAD]; 1 active inflammatory bowel disease; 1 reported a previous adverse reaction to a probiotic). Eighty-seven (34.4%) patients were eligible to participate in the pilot study but 8 of these were either confused or not available (in theatre or undergoing investigations). Therefore, the study design was explained to 79 patients (31.2% of total admissions) and 58 (73.4%) stated that they would have agreed to participate in this study.

We will monitor the number of participants reaching study endpoints in each hospital every 3 months. The ethical permission secured for the study included all hospitals within each health authority providing an ability to extend recruitment if needed.

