**Methods:**

This study aims to test the hypothesis that administration of a probiotic comprising two strains of lactobacilli and two strains of bifidobacteria alongside antibiotic treatment prevents antibiotic associated diarrhoea. We have designed a prospective, parallel group trial where people aged 65 years or more admitted to hospital and receiving one or more antibiotics are randomly allocated to receive either one capsule of the probiotic or a matching placebo daily for 21 days. The primary outcomes are the frequency of antibiotic associated and *C. difficile* diarrhoea during 8–12 weeks follow-up. To directly inform routine clinical practice, we will recruit a sufficient number of patients to demonstrate a 50% reduction in the frequency of *C. difficile* diarrhoea with a power of 80%. To maximize the generalizability of our findings and in view of the well-established safety record of probiotics, we will recruit a broad range of medical and surgical in-patients from two different health regions within the UK.

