### Statistical analysis

Primary outcomes will be analysed with standard methods for a binary outcome. Risk difference and odds ratio between two groups and their 95% confidence intervals for AAD and CDAD will be estimated. In addition, covariate adjustment analysis that includes the relevant covariates (such as age, gender, specific antibiotic, centre) will be performed. To explore whether prevention strategies should be provided to all patients or just those at high risk of diarrhoea, we will assess probiotic efficacy according to known or potential risk factors for AAD and CDAD as described previously. Sub-group effects will be identified by inspection of interaction terms, and these will be interpreted in light of power relative to main effects and supporting evidence of mechanism [31]. All analyses will be performed using SAS PROC PLAN Version 9.1 (SAS Institute Inc., Cary, NC, USA).

There are few tools that are validated for measuring QoL in older people and none specifically targeted at treatment-induced diarrhoea. We will use the generic measures EQ-5D and the York SF12 [32] to understand the broader health impact related to treatment-induced diarrhoea and facilitate cost-effectiveness analysis.

Health economic analysis will be undertaken from the perspective of the UK NHS. Resources utilised by each participant will include the cost of the probiotics, staff time involved in administering probiotics, treatment of adverse events, assessment of cases of diarrhoea (stool collection and culture/toxin assay, endoscopy) and the costs of dealing with and treating diarrhoea such as laundry, antibiotics, increased hospital stay and co-morbidities. Unit costs will be determined from discussion with relevant clinicians and finance department staff as well as from recognised published information.

Cost differences between the probiotic and placebo group will be determined and used in conjunction with differences in outcomes between groups in undertaking a cost-consequences analysis. Cost per case of diarrhoea averted will be the primary outcome measure. Sub-group analyses will determine the relative cost-effectiveness of preventative strategies in different risk groups. In addition, a cost-utility analysis will be undertaken based on the differences in costs between the two groups and in quality-adjusted life years derived from responses to the EQ-5D questionnaire.

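### The recruitment target of 2,974 is 2,478 × 1.20, so it covers about 16.7% loss and not the 10% plus 10% it is said to allow for (minor arithmetic error)

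*Protocol article*

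**What the plan says.** All the figures are in the section Sample size and recruitment of the protocol article. The planning rates are introduced with "Conservatively, we expected ADD to occur in 20% and CDAD in 4% of participants allocated to the placebo group" (the AAD abbreviation is transposed there). The effect to be detected is a halving of CDAD, from 4% to 2%, "with 80% power at the 5% significance level". For this the article says the trial "would require 2,478 subjects (1,239 in each group; 1:1 allocation"). The allowance for losses follows: "To allow for 10% drop-outs and 10% loss to follow-up due to deaths unrelated to diarrhoea, we plan to recruit 2,974 participants".

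For AAD, the same number before losses is said to give "a power of 90% to detect a 25% reduction in ADD (i.e. 15% frequency) in the probiotic group". The Methods part of the Abstract repeats the 80% power commitment for CDAD. Under Statistical analysis the test is described only in general terms: "Primary outcomes will be analysed with standard methods for a binary outcome".

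**The concern.** The same paragraph gives the number required, the expected losses and the number to recruit, so the three should agree. They do not. Multiplying the requirement by 1 + loss is a common slip, because the loss acts on the number recruited and not on the number required. The requirement must therefore be divided by 1 − loss.

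CDAD is the rarer of the two co-primary outcomes and is the one that sets the sample size, so any shortfall falls on the comparison with least margin. The planned recruitment rate has no slack to absorb it: about 124 per month for 24 months is 124 × 24 = 2,976, which matches the stated target.

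**Working it through.** **Inputs** (all from Sample size and recruitment): CDAD 4% on placebo and 2% on probiotic; 5% significance, taken as two-sided because the article does not say and two-sided reproduces its figure; 80% power; 1:1 allocation; losses of 10% and 10%; target 2,974.

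**1. Reproduce the requirement.** With pooled variance under the null, mean rate 0.03 and difference d = 0.02:

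n₀ = [1.960 × √(2 × 0.03 × 0.97) + 0.8416 × √(0.04 × 0.96 + 0.02 × 0.98)]² / 0.02² = 1,140.8, so 1,141 per arm without correction.

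With the continuity correction, n = (n₀/4) × [1 + √(1 + 4/(n₀d))]² = (1,140.8/4) × [1 + √(1 + 4/22.82)]² = 1,238.8, so 1,239 per arm and 2,478 in total. This is an exact match. Other usual variants do not match (per arm: unpooled 1,139; arcsine 1,110; one-sided 899; one-sided with correction 997).

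**2. Reproduce the target.** 2,478 × 1.20 = 2,973.6, rounded up to 2,974. This also shows that the two 10% losses were added.

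**3. Apply the stated losses to the target.**

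| Reading of the losses | Left from 2,974 | Short of 2,478 by | Target needed |
|---|---|---|---|
| Added, 20% | 2,974 × 0.80 = 2,379 | 99 | 2,478/0.80 = 3,098 |
| Compounded, 19% | 2,974 × 0.81 = 2,409 | 69 | 2,478/0.81 = 3,060 |

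The loss that 2,974 does cover is 1 − 2,478/2,974 = 16.7%.

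**4. Power at the numbers left.** For CDAD on the corrected basis, power = Φ{[d − 1/n − 1.960 × √(0.0582/n)] / √(0.0580/n)}. The uncorrected version omits 1/n. At n = 1,189.5 per arm, the corrected value is Φ{(0.02 − 0.00084 − 0.01371)/0.00698} = Φ(0.780) = 78.2%.

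| Total analysed | CDAD, corrected | CDAD, uncorrected | AAD 20% vs 15%, corrected | AAD, uncorrected |
|---|---|---|---|---|
| 2,478 | 80.0% | 83.1% | 89.7% | 90.6% |
| 2,409 | 78.8% | 82.1% | 88.8% | 89.8% |
| 2,379 | 78.2% | 81.6% | 88.5% | 89.5% |

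Fisher's exact test lies between the two CDAD columns: 81.0% at 1,239 per arm, 80.1% at 1,204 and about 79.5% at 1,189 to 1,190.

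**The case against.** A reader might infer that the trial is underpowered for CDAD, full stop. The article does not support that. It names no test for the primary outcomes, and an uncorrected chi-square test, which its general wording permits, still has about 82% power after the stated losses. On that basis the requirement would be only 2 × 1,141 = 2,282, and 2,379 exceeds it. This point stands and limits the claim about power. It does not rescue the target: the article states 2,478 as the requirement, and 2,974 does not deliver 2,478 after the stated losses, whichever test is used.

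Three further points soften the consequence:

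- Participants withdrawn for pancreatitis or severe illness stay in the intention-to-treat analysis. With daily review in hospital and weekly contact after discharge, diarrhoea before a later drop-out or death would often already be recorded. The effective loss could therefore be below 20%. But 20% is the allowance the plan itself chose.
- Endpoints are monitored every three months, and ethical permission covers all hospitals in each health authority, so recruitment could be extended. That is a contingency and does not correct the stated figure.
- The event rates and the two loss rates are round planning values. A shift of under two points in power is slight beside that uncertainty. This is fair, and it is why the point is minor.

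That the article does not mention the continuity correction is no error. A condensed article commonly leaves such detail to the full protocol or analysis plan.

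**Conclusion.** The point holds as a minor arithmetic error. The target of 2,974 falls short of the losses it is said to allow for, by 99 participants if they add and 69 if they compound; it covers about 16.7%. This compares figures within one paragraph and depends on no choice of test.

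The effect on power does depend on the test. On the basis that reproduces the article's own 1,239 per arm, CDAD power is about 78% instead of 80%, a loss of 1.2 to 1.8 points. Without the correction it stays above 80%. AAD power changes by about one point, which is immaterial. These figures assume the stated event rates, a two-sided 5% level, equal loss in both arms and no outcome information from those lost. The design, allocation and analysis are unaffected.

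**What to change.** Correct the sentence in Sample size and recruitment in one of two ways:

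- state that 2,974 allows for about 16.7% total loss; or
- keep the 10% plus 10% allowance and restate CDAD power as about 78% on the continuity-corrected basis, bringing the 80% in the Abstract into line.

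Either is a change of wording only, with no effect on conduct.

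If the sponsor preferred to hold 2,478 after the stated losses, the target would be 3,060 (compounded) to 3,098 (added). That is 86 to 124 more participants (2.9% to 4.2%), or at most about one month at the planned 124 per month. The size of the effect does not oblige this.
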